### Study Participants

The effect of the *KaziKidz* teaching material will be evaluated in 1 randomly selected class in grades 4, 5, and 6 (=intermediate phase) in each of the 8 study schools (interventions are randomly assigned to any of the 4 northern area or 4 township schools) even though *KaziKidz* teaching material will be offered to all classes in grades 1 to 7 as part of the life skills and life orientation courses in the school curriculum.

For *KaziHealth*, all teachers from the 8 schools will be invited to participate in the program. All participating teachers will undergo the full health risk assessment, and teachers at the intervention schools will have the option to participate in the 20-week intervention. The teachers from the control schools will be offered the intervention program after the completion of the study.

### School Selection, Participant Recruitment, and Written Informed Consent

South African public schools are classified into 5 groups, with quintile 5 representing the least poor and quintile 1 representing the poorest. The quintiles are determined through the national poverty table developed by the treasury [38]. Areas are being ranked on the basis of income levels, dependency ratios, and literacy rates in the area. The quintile ranking of a school determines the no-fee status of the school and the amount of money that a school receives from the government, with the poorest schools receiving the greatest per-child allocation. Approximately 200 principals and/or representatives from 349 quintile 3 primary schools (no-fee paying schools) of the Nelson Mandela Bay Municipality attended information-sharing sessions at the Eastern Cape Department of Education in October 2018. The intention was to be inclusive and invite as many interested principals as possible to inform them of the study. A total of 64 responses were received from interested schools; however, only 8 of the responses (representative of typical quintile 3 primary schools) matched the following criteria:

Geographical location and representation of the target communities: *township areas* inhabited predominantly by black African people and the *northern areas* inhabited by predominantly colored people; both these communities needed to be represented equally.Spoken language (IsiXhosa, Afrikaans, or English).Commitment by school principal to support the project activities.

The school authorities will be informed about the project and asked for their interest and consent. Interested schools will be visited, and the investigators will consult with the school administrators to find out if the school environment is conducive for conducting the study. Principals and teachers from selected schools will be informed about the objectives, procedures, and potential risks and benefits of the study. Teachers, children, and parents or guardians will be informed and teachers and children invited to participate in the study. Before enrollment, a participant information sheet will be provided in English, IsiXhosa, or Afrikaans (local languages) to all potential participants and in case of the children, their parents or guardians. For the evaluation part of the study, oral assent of each participating child will be obtained, whereas written informed consent will be obtained from parents or guardians and teachers. Participation is voluntary; hence, children and teachers can withdraw anytime without any further obligations.

Potential participants will be enrolled in the project for evaluation purposes if they meet the following inclusion criteria: (1) are willing to participate in the study, (2) have a written informed consent (for children by a parent or guardian), (3) are not participating in other clinical trials during the study period, and (4) do not suffer from severe medical conditions, as determined by qualified medical personnel. Approximately 1000 grade 4 to 6 school children, aged 9 to 13 years, and approximately 60 teachers from 8 primary schools will be recruited during the *KaziBantu* baseline survey in early 2019.

### Assessment Methods

Primary outcomes for the *KaziKidz* testing battery include (1) anthropometric and clinical examinations, (2) physical fitness and self-reported and objectively assessed activity, (3) cognitive and academic performance, and (4) questionnaire for assessment of psychosocial health. Primary outcomes for the *KaziHealth* testing battery include (1) anthropometric and body composition assessments, (2) clinical examinations, (3) self-reported and objectively assessed physical activity and physical fitness, and (4) questionnaire results from psychosocial health assessment. Further measures include diet and nutritional analysis with the 24-hour dietary recall. Secondary outcomes for both tests are gender, ethnicity, SES, age, weight, and height. Figure 7 summarizes the assessment methods to be utilized in this study. For baseline and follow-up surveys, the same scientifically recognized procedures will be selected and conducted by professional staff, adhering to standardized, quality-controlled protocols.

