### Sample Size and Randomization

Assuming that the prevalence of obesity varies across schools according to a log-normal distribution with a mean value of 3% and a SD of 2%, 125 children per school in each of the 8 schools would provide a prevalence estimate between 1.5% and 5% with a probability of 95%. Under this assumption, 95% of school-specific prevalence would range between 0.8% and 8.2%. Hence, our aim is to recruit 125 children per school.

The power calculation for the intervention study is based on the change in a quantitative outcome variable from baseline to follow-up. We denote the SD of its change across schools and children by sigma (σ). Assuming an intervention effect size of 0.5 x σ and an intraclass correlation of .04 for the clustering of individual changes within schools (corresponding to a random effect SD of 0.2 x σ), 400 children in the 4 intervention schools (ie, 100 children per school) participating in baseline and follow-up, and 400 children in the 4 control schools would provide over 85% power to observe a statistically significant difference in the mean change of the respective outcome variable between intervention and control schools at the 5% level.

Enrollment of schools will be done by the local research team. To prevent contamination of the intervention effects, schools rather than classes were randomized in January 2019. Before randomization, schools were divided into 2 geographic groups; namely, township areas and northern areas, each containing 4 schools. Township areas are predominantly inhabited by black Africans and northern areas by colored people (after an apartheid-era classification, which refers to people from a multiracial ethnic background and can include persons of Khoi and San origin).

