#### Data Collection and Statistical Analysis

The following data will be collected: (1) quantitative data on blood pressure, glycated hemoglobin and blood lipids, anthropometry and levels of physical fitness, cognitive performance and psychosocial health, (2) SES and demographic data, and (3) qualitative data on the feasibility and acceptability of the intervention measures implemented through FGDs. Quantitative data will be entered twice and cross-checked using EpiData version 3.1 (EpiData Association; Odense, Denmark). Cleaned data will be transferred to STATA version 13.0 (STATA Corp, College Station, TX, United States of America). Questionnaire data will be collected using the software package EvaSys (Survey Automation Suite, version 7.1) and analyzed with STATA.

Clinical and anthropometric indicators, physical fitness, cognitive performance, and psychosocial health values will be summarized by their mean and SD at normal distribution and otherwise by their median and interquartile ranges. Questionnaire information on psychosocial health will be expressed as a percentage.

For the analysis of cross-sectional and longitudinal associations, mixed linear or mixed logistic regression models will be used, depending on the type of outcome variable. These models will be adjusted for clustering within classes and schools using random intercepts. In analyses of cross-sectional associations, the models will include personal characteristics of children, such as gender and age, SES of parents or guardians, and other potential confounders of the associations of interest. Models assessing intervention effects will additionally include 3 indicator variables, as defined at the level of schools, 1 for schools of the intervention arm, 1 for schools receiving teacher workshops, and 1 for schools receiving teacher coaching. In addition, these models may include the value of the respective outcome variable at baseline. As intervention effects may also depend on the child’s initial characteristics, stratified analyses and analyses with interaction terms will be performed. Potential effect modifiers to be tested include gender, age, SES, ethnicity, health status, and physical fitness at baseline.

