The primary objectives of the statistical analyses are (1) to assess the physical fitness of the participants and their associations with cognitive performance and psychosocial health at the beginning and over the course of the intervention, and (2) the effect of interventions on disease status and other health parameters. The secondary objective is to assess the feasibility and acceptability of the health interventions, as determined by FGDs.

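### Whole measurement domains are declared primary and no primary endpoint is named, while power is stated for one unnamed variable and baseline characteristics are labelled secondary outcomes

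*Protocol article*

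**What the plan says.** All references are to the protocol article.

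- **Primary outcomes, children** (Assessment Methods): "Primary outcomes for the *KaziKidz* testing battery include (1) anthropometric and clinical examinations, (2) physical fitness and self-reported and objectively assessed activity". Cognitive and academic performance and a psychosocial questionnaire complete the four domains.
- **Primary outcomes, teachers** (same section): "Primary outcomes for the *KaziHealth* testing battery include (1) anthropometric and body composition assessments, (2) clinical examinations". Activity with fitness, and psychosocial questionnaires, complete the four. Teachers have no academic domain. Dietary recall is set apart as a further measure.
- **Secondary outcomes, both populations** (same section): "Secondary outcomes for both tests are gender, ethnicity, SES, age, weight, and height".
- **Power** (Sample Size and Randomization): "The power calculation for the intervention study is based on the change in a quantitative outcome variable from baseline to follow-up". The target is a "statistically significant difference in the mean change of the respective outcome variable between intervention and control schools at the 5% level". The variable is not named.
- **Comparison** (Study Design): the primary contrast is the 4 intervention schools against the 4 control schools, with the coaching and workshop contrasts secondary. No endpoint is attached to it.
- **Use of the same characteristics in the models** (Data Collection and Statistical Analysis): gender, age and SES are adjustment variables in the cross-sectional models, and "Potential effect modifiers to be tested include gender, age, SES, ethnicity, health status, and physical fitness at baseline".
- **Objectives** (same section): "The primary objectives of the statistical analyses are (1) to assess the physical fitness of the participants and their associations with cognitive performance". This first objective also covers links with psychosocial health. The effect of the interventions on disease status and other health parameters is the second primary objective.

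**The concern.** A primary outcome tells the reader which single result, or which short controlled set, decides whether the trial succeeded. Here the primary tier covers most of what is measured, and the secondary tier holds only baseline characteristics plus two measurements that are already in the primary tier. The stated hierarchy therefore separates nothing.

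Three things follow.

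1. The 5% level and the power apply to one variable, and the text does not say which. They cannot be carried over to a claim that may rest on any of many variables.
2. The outcome list contains variables that the intervention cannot change, which contradicts the role the analysis section gives them.
3. An association of fitness with cognition and psychosocial health, which randomisation does not protect, has the same primary rank as the randomised effect.

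If this stands until follow-up is analysed, choosing one variable as the main result can no longer be shown to be independent of the data.

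**Working it through.** **1. Consistency of the outcome labels**

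| Variable | Assessment Methods | Elsewhere in the article |
|---|---|---|
| Gender, age, SES | secondary outcome | covariate and effect modifier (analysis section) |
| Ethnicity | secondary outcome | effect modifier (analysis section) |
| Weight, height | secondary outcome | measured under Anthropometric Measurements, a primary domain for children; body weight and height are also in the teachers' anthropometry |

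Gender, ethnicity and age do not respond to treatment, and household SES is not a plausible target of a 36-week school programme. Weight and height sit in both tiers.

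**2. The stated power**

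Inputs from Sample Size and Randomization: effect 0.5σ, intraclass correlation 0.04, 4 schools per arm, 100 children per school, 5% level (two-sided assumed).

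- Design effect: 1 + (100 − 1) × 0.04 = 4.96
- Effective number per arm: 400 / 4.96 = 80.6
- Standard error of the difference, in units of σ: √(2 / 80.6) = 0.1575
- Standardised effect: 0.5 / 0.1575 = 3.175
- Power: Φ(3.175 − 1.960) = Φ(1.215) = 0.888

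This agrees with the stated figure of over 85%. It is the power for **one** endpoint tested at 5%.

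**3. How many child variables the primary domains hold**

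My count, from the KaziKidz assessment sections:

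- Anthropometry, 5: z-scores for BMI, height and weight; waist circumference; waist-to-hip ratio
- Clinical, 9: systolic and diastolic blood pressure, six lipid measures, HbA1c
- Fitness, 2: VO2max, grip strength
- Activity, 2: accelerometer, self-report
- Academic, 1: exam sum score
- Psychosocial, 4: KIDSCREEN-10, stress, school satisfaction, academic self-concept

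Total: 5 + 9 + 2 + 2 + 1 + 4 = 23. The plausible range is 18 to 26, depending on how derived or overlapping variables are treated. The article gives no such number. The teacher battery would add more.

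**4. Illustration: each variable tested at 5%, no true effects**

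- Independent tests: 1 − 0.95^23 = 0.693 (0.603 for 18 variables, 0.736 for 26)
- Expected false positives: 23 × 0.05 = 1.15
- Equally correlated normal test statistics, with ρ assumed because the article gives none:

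| ρ | 18 variables | 23 variables | 26 variables |
|---|---|---|---|
| 0.3 | 51% | 58% | 62% |
| 0.5 | 40% | 45% | 48% |
| 0.7 | 28% | 31% | 32% |

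**5. Power if the level is divided**

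Power = Φ(3.175 − z), with z the two-sided critical value at 0.05/K.

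| K | level | z | power |
|---|---|---|---|
| 1 | 0.05 | 1.960 | 88.8% |
| 2 | 0.025 | 2.241 | 82.5% |
| 3 | 0.0167 | 2.394 | 78.3% |
| 23 | 0.00217 | 3.065 | 54.4% |

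The rows for 2 and 3 are also the least favourable case under Holm, whose first step uses 0.05/K. All rows use the normal approximation, which treats 8 schools as a large sample. On a t test with 6 degrees of freedom the single-endpoint power is 75.4%; that is a separate matter and is not needed here.

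**The case against.** The strongest reply is that this is a condensed article. A multiplicity rule or testing order may sit in an analysis plan that is not shown, and the 5% level appears only in the sample size section, as a planning value. That stands: the absence of a multiplicity rule is not the point, and the article does not say that each variable will be tested at 5%. The point rests on the hierarchy that the article does state.

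The figure of 69% also deserves the criticism that it assumes independence. Non-HDL cholesterol and the cholesterol ratio derive from total and HDL cholesterol, BMI shares weight and height with the other z-scores, and waist circumference enters the waist-to-hip ratio. The correlated range is the more credible illustration.

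A reader might infer more than the documents support:

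- **That the trial has no confirmatory comparison.** Study Design fixes the primary contrast, and the analysis section gives a mixed model with school-level intervention indicators. What is missing is the endpoint.
- **That the same domains are primary in both populations, or that everything measured is primary.** Academic performance is primary for children only, and dietary recall is set apart.
- **That the randomised effect is not a primary objective.** It is the second of the two listed. The difficulty is that the association has equal rank.

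Finally, mislabelling the baseline characteristics changes no planned model, because the analysis section already uses them properly. That is right. It remains an error in the outcome list, and it leaves the secondary tier without usable content.

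**Conclusion.** The point holds in this form: the article declares domains, not an endpoint, as primary in each population; it powers one variable without naming it; and it lists baseline characteristics as outcomes. The sections on design, sample size and objectives do not repair this.

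The contradictions over labels and the unnamed endpoint need no assumption. The size does. It rests on a count of about 23 child variables (18 to 26), on each being tested at 5%, and on assumed correlations. On that basis the chance of at least one false positive is about 31% to 58% for 23 variables, with 69% as the independence case. The stated power of over 85% is sound, by the normal approximation, for one endpoint at 5%. It does not extend to the whole primary tier, where Bonferroni over 23 would leave about 54%.

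This should be settled before follow-up data are seen. The article places the follow-up survey in September to October 2019, after the time of writing.

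**What to change.** Before follow-up data are seen:

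1. Name one quantitative primary outcome for children, and tie to it both the comparison in Study Design and the power statement. Alternatively, name a short primary list tested with Holm and restate the power at the adjusted level; by the table above, two endpoints already give 82.5% in the least favourable case.
2. Name one primary outcome for teachers. Say plainly that the power statement covers children only and that none is given for the approximately 60 teachers.
3. Make the remaining battery measures secondary.
4. Relabel gender, ethnicity, SES and age as baseline covariates or effect modifiers, and place weight and height under anthropometry only.
5. State the randomised intervention effect as the confirmatory objective, and mark the fitness association analyses as non-confirmatory.

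The cost is wording, with no new data or participants. The sponsor gives up calling every battery item primary, and with a short list accepts lower power per endpoint.

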**Figure 7 figure7:**
[figure not shown]
Measurements and tests performed among school children (a) and teachers (b) in the *KaziBantu* study.

### 
*KaziKidz* Assessment Protocol

#### Anthropometric Measurements

The anthropometric measurements are as follows:

For each participant, body weight and height will be measured by standing on a digital weighing scale and against a stadiometer with back erect and shoulders relaxed, recorded to the nearest 0.1 kg and to the nearest 0.1 cm, respectively. Age- and gender-specific height or height-for-age and weight-for-age z-scores will be calculated from the current Centers for Disease Control and Prevention (CDC)/World Health Organization (WHO) growth reference data. Body mass index (BMI) and specific z-scores will be calculated as follows: (1) BMI=weight (kg)/height (m)^2^, (2) BMI for children older than 5 years, an indicator for weight-for-height proportion (WHO growth reference for children older than 60 months) [20], (3) height-for-age, an indicator of growth disorders (WHO growth reference for children older than 60 months), and (4) weight-for-age.A measuring tape will be used to determine the waist circumference of the participant, measured midway between the rib cage and the iliac crest on a gender-appropriate basis. After measuring the hip circumference, the waist-to-hip ratio will be calculated, a risk indicator for heart disease (ie, the smaller the waist in comparison with the hips, the lower the risk of heart disease) [39].

#### Questionnaires

To gather information on children’s social and demographic background, SES, self-perceived stress, school satisfaction, academic self-concept, self-reported physical activity behavior, and general health status, the following questionnaires will be applied:

The demographic data and SES of each participant will be determined.The KIDSCREEN-10 will be implemented to determine children’s physical and psychological well-being, moods and emotions, self-awareness, autonomy, parenting and family life, financial resources, peers and social support, school environment, and bullying. The questionnaire comprises 10 points and has proven to be a valid tool for assessing the psychosocial health of children aged 8 to 18 years [40-42].A total of 3 items from the Health Behavior in School-age Children survey [43] will be used to assess individual perceived stress, school satisfaction, and academic self-concept. Learners will be asked how they perceive the pressure, including from homework, related to school [44]. To estimate school satisfaction, children will be asked to respond to the question: *How do you feel about school at present*?Children will also be asked questions about their physical activity behavior, including sports participation, being physically active during school hours, and type of play during school hours and in their free time. Information will be collected over a 7-day period. The questions are adjusted using the Physical Activity Questionnaire for Children, an instrument used to gain insights into general levels of physical activity throughout the elementary school year for children attending grades 4 to 8, aged between 8 and 14 years [45].

#### Clinical Examinations

Clinical examinations will include:

The children’s health review will include a detailed history and physical examination. Self-reported health status will focus on intestinal symptoms, including abdominal pain and changes in bowel movements. In addition, we will assess children’s evolution of cognitive and physical development. The physical examination is directed toward evidence of anemia (eg, conjunctival pallor), abdominal conditions (eg, hepatomegaly and splenomegaly), and evidence of pulmonary hypertension (eg, jugular venous pressure and cardiac auscultation).Regarding high blood pressure detection, each participant’s blood pressure will be measured 3 times after the participant has been seated for 5 min with a calibrated Omron digital blood pressure monitor (Omron M6 AC model; Hoofddorp, The Netherlands). The cuff is wrapped around the left arm so that only a finger can fit between the cuff and arm. The bottom of the cuff is placed about 4 cm above the elbow with the palm facing up, while the blood pressure is taken. For children, a cuff size of 17 to 22 cm will be used (Omron CS2 Small Cuff; Hoofddorp, The Netherlands). As the first measurement often results in higher values, the average of the second and third measurements will be utilized to estimate systolic and diastolic blood pressure. To analyze the data, children will be categorized into a normotensive, prehypertensive, or hypertensive group, based on percentiles, taking into account the age, sex, and height of the children (normotensive: less than the ninetieth percentile; prehypertensive: at or above the ninetieth percentile to at or below the ninety-fifth percentile; and hypertensive: at or above the ninety-fifth percentile).For determination of the full blood lipid profile (total cholesterol, low-density lipoprotein cholesterol [LDL-C], high-density lipoprotein cholesterol [HDL-C], triglycerides, non-HDL cholesterol [non-HDL], cholesterol high-density lipoprotein ratio [C-HDL ratio]), glycated hemoglobin (HbA1c) affecting diabetes, and a point-of-care (POC) instrument (Alere Afinion AS 100 Analyzer, Abbott Technologies; Abbott Park, United States of America) will be used, providing results within 8 min. The HbA1c level reflects the average plasma glucose concentration levels over the last 8 to 12 weeks. After the participant’s fingertip is cleaned with an alcohol swab, a nurse will prick the fingertip with a safety lancet and gently squeeze out 2 drops of blood. The first drop will be wiped away, and the second drop will be collected for analysis. Before the assessments, all machines will be tested and calibrated with controls.
